## Abstract

**Background:**

One of the largest school feeding programs in the world is the National School Feeding Program of Brazil. However, results from the 2012 National School Health Survey indicated that only 22.8% of 9th grade students in Brazilian public school system consumed school meals. The literature presents few studies aiming to promote healthy food consumption in the school environment from interventions, which found inconclusive results. Thus, this study aims to present a protocol to evaluate the effectiveness of multi-component school-level interventions to increase adherence and acceptance to school feeding.

**Methods:**

School-based multi-component clinical trial with students from 4th-9^h^ grade from 3 municipal schools of Sumidouro, Rio de Janeiro, Brazil, in 2019. The study design will be parallel, with 3 arms: Control group (without intervention); Intervention group 1 (changes in school environment) and Intervention group 2 (changes in menu and school environment). Interventions in the environment will be based on the principles of choices architecture and, the modification in the dishes that make up the menus offered to the students, on the factors that contribute to poor adherence and acceptance to school feeding, identified by focus groups. Adherence to school feeding will be assessed through a specific question in the questionnaire directed to the frequency of consuming school meals in the week, applied by researchers in three moments. Acceptance will be assessed from the acceptability test application with dishes served to students during the year. Statistical analyses will be performed using generalized linear models, which will be used to assess the impact of the intervention, and will include 3 main variables: intervention, time and the intervention x time interaction.

**Discussion:**

This study will investigate if the impact of the implementation of interventions in the environment and in the dishes served to students may increase adherence and acceptance to school feeding. Positive results could show the effect of implementing interventions throughout Sumidouro’s public school system, as well as throughout the country, aiming to improve the consumption of school meals.

**Trial registration:**

Brazilian Registry of Clinical Trials, RBR-7mf794. Date of registration: December 27, 2018.

## Background

The world has made progress in reducing extreme poverty in the last few years. In 2015, there was a reduction of over a billion people living in this situation, in comparison to 1990. Progress was driven by strong global growth and the growing wealth of many developing countries [1].

Although an economic advance on the world stage is observed, the United Nations Food and Agriculture Organization has published in its report that since 2015 the number of undernourished people has increased. In 2018, more than 820 million people worldwide were still hungry. Among these, 34,7 million were located in Latin America, highlighting the great challenge of meeting the goal number 2 of the Sustainable Development Goal (SDG), which predicts zero hunger by 2030 [2].

This scenario is more disturbing when looking at the population of students. The United Nations World Food Program estimates that, throughout the world, 66 million people go to school hungry [3]. School feeding programs are the most prevalent social protection network in the world [4]. It is a recognized strategy for improving student nutrition and health, as well as increasing access to education and school attendance, reducing inequalities in education and improving students’ performance. When linked to local agriculture, school feeding also strengthens the region’s economic development by cooperating with small producers [5].

In Brazil, the National School Feeding Program (PNAE) was created in the 1950s and is characterized as the country’s longest-running public policy on food and nutrition security, being considered one of the largest, most comprehensive and long-lasting school feeding programs in the world, only behind to India [5–7]. According to the World Food Program report, more than 40 million children and adolescents benefit daily from PNAE in Brazil [6]. In 2019, the Brazilian federal government had a budget of 3.5 billion reais (approximately 877 million dollars) to support school meals in basic education, serving students in kindergarten, elementary, high school and youth and adult education. This amount is passed on directly to the states and municipalities (executing entities), that complement it with their own resources [8].

However, providing food allowance for students enrolled in the public school system does not guarantee that adherence to the program is satisfactory in Brazil. Results from the 2012 National School Health Survey (PeNSE) indicated that only 22.8% of 9th graders in public schools consumed school meals at least 3 days a week [9]. In a new edition from PeNSE, conducted in 2015, revealed that only 31.3% of Brazilian students enrolled in the 9th grade of public schools consumed school meals on at least 3 days of the week [10], being classified as low adherence to school feeding [11].

Acceptance of school meals (approval of the dish offered) is another important factor, once it reflects the quality of services provided by schools and refers to the average preference of foods offered by them [12]. According to the National Education Development Fund (FNDE), menus must be prepared by nutritionists, based on students’ eating habits, and should have 85 to 90% acceptance [12, 13]. Silva et al. (2013), in a study conducted with 1448 students from the state school system of Minas Gerais, Silva et al. (2013) observed that the effective acceptance, answers considered as “excellent” and “very good”, reached only 28.8% [14].

In an integrative literature review, which aimed to identify the factors that influence the adherence and acceptance to school meals among Brazilian students, it was observed that, the most relevant ones were socioeconomic variables, nutritional status, age, presence of competitive foods in the school environment, behavioural factors such as changes in dietary practices and choices, as well as inadequate preparation for eating habits [15]. In this context, the school has the role of educating, as well as making individuals aware of the countless possibilities of healthy consumption, more attentive to their practices and eating habits [13, 16–18].

Systematic review indicated that school-based interventions have the potential to improve dietary behavior. Most studies provided nutrition education to promote healthy diet, but the most effective intervention programs have multiple components. Only five studies conducted with multi-component interventions showed positive effects, such as increased preferences for healthy food and decreased daily consumption of sweetened carbonated drinks, fast food eating behavior score, frequency of fast food consumption in general and in schools, besides the reduction in fried food consumption, soda intake, and snacks high in fat, sugar, and salt [19].

Previously, Van Cauwenberghe et al. had reported the moderate evidence that educational interventions conducted by the teachers in adolescents could improve dietary behavior and inconclusive evidence of effect of environmental interventions that consisted of adapting or increasing the availability of healthy food [20]. According to Verstraeten et al., few interventions targeted the school environment, which is pointed as a challenge because of the type and complexity of changes required [19]. So, due to the complex nature of eating behavior, multicomponent interventions may contribute to influence the food supply, acting as a promising population-based approach to promote health. Furthermore, improving the community food environment is important, especially in low-income areas that present increased access to unhealthier foods [21].

Choices architecture based strategies is a tool that can change behaviour and lead children’s and adolescents’ choices for a healthier life [22]. The concept of choices architecture can be defined as an intervention that preserves freedom of choice, without coercion or obligation, only influencing people’s behavior in a predictable way for decision making [22, 23]. In recent years, there has been an increase in both interest and importance in changing children’s eating behavior for healthier choices [24]. In the school environment, these strategies can be implemented in cafeterias, making it convenient to eat healthy foods [25]. However, there are few studies in the literature that aimed to promote the consumption of healthy food in the school environment through interventions based on choices architecture, and such studies found inconclusive results [26].

Thus, studies are needed to evaluate intervention strategies to increase adherence and acceptance of school feeding. Considering that adolescents are highly susceptible to environmental influences, it is suggested that interventions carried out in the school feeding environment and in the dishes served to the students present themselves as an appropriate tool to promote an increase in adherence and acceptance of school feeding.

## Methods

### Study design

This is a multi-component school-based, clinical trial called PAPASS, which means “Professionals and Students for Healthy Eating in Sumidouro”. PAPASS is a study aimed at increasing adherence and acceptance of school meals, which will be conducted in the 2019 school year in 3 public schools in the city of Sumidouro, Rio de Janeiro, Brazil. All students from 4th to 9th grade, morning and/or afternoon shifts from the 3 selected schools will be invited to participate in the study.

The study design will be parallel, with 3 arms: (1) Control group (without intervention); (2) Intervention group 1 (changes in the school environment) and (3) Intervention group 2 (changes in the menu and school environment) (Fig.1). To allocate interventions, schools will be numbered and randomly allocated to each group using opaque envelopes by people who are not involved in PAPASS.

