### Data collection at school

Data on the characteristics of the study population (age, gender and skin color/ race), anthropometric measures, socioeconomic data, physical activity practice, sedentary habit, breakfast habit, food intake and adherence to school feeding will be collected in three moments (baseline - March, half of the school year – August, and end of the school year - November), using a structured questionnaire applied by trained researchers. Acceptability tests will be performed bimonthly, in order to include all menus established in the schools participating in the study.

Adherence will be assessed through a specific question in the questionnaire directed to the frequency of school meals consumptionin the week, with the options: never, once a week, twice a week, three times a week, four times a week or all days. Students who consume the food offered 3 or more times a week will be considered as adhering to the school feeding program [9]. Each adolescent will be assessed in 3 moments: at baseline - at the beginning of the school year; the second - at half of the school year; and the third - at the end of the school year. In order to avoid follow-up losses, schools will be visited 4 times at each moment of data collection (Table 1).

**Table 1 Tab1:** Intervention components, description and assessment

Intervention components	Description	Assessment
Adherence to school meals	- Placement of posters on cafeteria walls and displays on tables with messages and/or images that encourage students to make healthier food choices; - The implementation of the use of tablecloths in the cafeteria with color images of fresh foods, accommodation of the fruits served in the school feeding in a prominent position, improving their visibility in an attractive way; - The equipment of the cafeterias, with the installation of a thermal distribution counter to guarantee the autonomy of food choice by the students, through a self-service system; - Placement of a banner with the daily dishes menu at the entrance of the cafeteria; application of footprints on the floor that playfully direct the adolescents to the cafeteria; - Changes in the dishes that make up the menu of the only school which will receive the two interventions (Intervention group 2).	A question about the frequency of school meal consumption, applied in 3 moments (baseline, half of the school year and end of the school year).

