### Intervention

The interventions will take place during the 2019 school year, beginning in April, in the two schools allocated to the intervention groups and will combine two strategies: modifications in the school environment and modifications in the menu offered by the school. Interventions in the environment will be based on the choices architecture principles proposed by Thaler & Sustein [23, 37, 38], and the interventions in the menu will be based on the factors that contribute to poor adherence and acceptance of school feeding, identified through a previously conducted focus groups with the lunch ladies (school food service employees) of the all 3 participating schools and the students of the school that will receive the two interventions (intervention group 2).

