## Statistical analysis

Statistical analyses for each outcome will be performed using generalized linear models that takes into account repeated measurements and missing data. The models will be used to assess the impact of the intervention and will include 3 main variables: intervention (intervention 1, intervention 2 or control school), time (treated as continuous, in months) and the intervention x time interaction. Data analysis will be performed using the SAS OnDemand for Academics (SAS Institute Inc., Cary, NC, USA).

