To date, no Brazilian studies have been identified in the scientific literature that have been conducted aimed at changes in the school environment and in the dishes that make up the menu offered to students from the public school system, with the aim of increasing adherence and acceptance to school feeding. To this end, the controlled trial of PAPASS multi-component intervention described in this protocol document will provide data on the effects of new intervention approaches, as well as combination of interventions.

We plan to disseminate the findings from this trial through: a community presentation to the participants involved in the study, presentations at relevant conferences for researchers and healthcare professionals, as well as in peer-reviewed publications.

The hypothesis that new approaches can contribute to increase adherence and acceptance of school meals by students, if accepted, will attest to the effect of implementing interventions throughout the public school system of Sumidouro, as well as the country, with the objective of improving the food consumption of the students.

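### With one school per arm, school-specific change during 2019 cannot be told apart from the intervention, so the stated conclusion for Sumidouro and the country does not follow

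*Protocol article*

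**What the plan says.** The Study design section describes a trial "which will be conducted in the 2019 school year in 3 public schools in the city of Sumidouro". It continues: "The study design will be parallel, with 3 arms", and "schools will be numbered and randomly allocated to each group using opaque envelopes". That is one school per arm. Two later places confirm it. Table 1 (Data collection at school) lists "Changes in the dishes that make up the menu of the only school which will receive the two interventions", and the Intervention section speaks of work "in the two schools allocated to the intervention groups", which leaves one control school.

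The Statistical analysis section plans "generalized linear models that takes into account repeated measurements and missing data", with terms for intervention, time (continuous, in months) and their interaction. The intervention variable has three levels, one for each school. The only dependence named is that of repeated measurements.

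The main Discussion says that the hypothesis, if accepted, "will attest to the effect of implementing interventions throughout the public school system of Sumidouro, as well as the country". The Discussion paragraph of the Abstract is softer: "Positive results could show the effect of implementing interventions throughout" the municipal system and the country.

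**The concern.** Allocation is by school, and there is one school in each arm. Arm and school are therefore the same variable, and any difference between arms is also a difference between schools. The baseline helps with differences that are stable. It does not help with a school whose adherence would have drifted during 2019 for its own reasons, such as a change of staff, competing foods nearby or a local event. The interaction term, which carries the intervention effect, contains that drift in full.

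Two things are at stake. The pupil-level p-values and intervals may be too optimistic by an amount that the data cannot reveal. And the article draws a policy conclusion for a whole school system, and for the country, from a comparison that includes no replication of schools within arms.

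**Working it through.** **Inputs from the Protocol article.** Three schools, three arms, allocation by school (Study design). Control adherence 37.21%, a 50% increase, 80% power, 5% significance, 109.4 pupils per arm, raised by 20% to about 132 (Sample size calculation). March baseline (Data collection at school) and intervention start in April (Intervention).

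**Assumed, because the article gives none.** School intraclass correlation (ICC) 0.02 to 0.05; cluster autocorrelation (CAC, the share of school variance that is stable over time) 0.8 to 0.9; within-pupil correlation ρ 0.3 to 0.5.

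**1. The plan's own figure.** With p1 = 0.3721, p2 = 1.5 × 0.3721 = 0.558 and a two-sided 5% level, the unpooled two-proportion formula gives

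(1.96 + 0.842)² × (0.3721 × 0.6279 + 0.558 × 0.442) / 0.186² ≈ 108.9 per arm.

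The pooled form gives 111.6. Both are close to the stated 109.4, and 109.4 × 1.2 = 131.3. The sample size is that of an individually randomised trial, with no allowance for school.

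**2. What the allocation alone can support.** Three schools can be assigned to three arms in 3! = 6 ways. For one contrast, the smallest randomisation p-value is 1/6 = 0.17 one-sided and 2/6 = 0.33 two-sided, however many pupils take part. A school-level comparison of two arms has 1 + 1 − 2 = 0 degrees of freedom, so school-to-school variation cannot be estimated.

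**3. What the baseline leaves behind.** Take the difference between two schools in change from baseline to one later wave, with pq = 0.3721 × 0.6279 = 0.2336.

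- Pupil-level variance: v = (2pq/109.4) × 2(1 − ρ).
- School-by-time variance: s = 4 × ICC × (1 − CAC) × pq.
- Ratio: s/v = ICC × (1 − CAC) × 109.4 / (1 − ρ), so pq cancels.
- True type I error of a test that uses v alone: 2 × [1 − Φ(1.96 / √(1 + s/v))].

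| ICC | CAC | ρ | s/v | True type I error |
|---|---|---|---|---|
| 0.02 | 0.9 | 0.3 | 0.02 × 0.1 × 109.4 / 0.7 = 0.313 | 0.087 |
| 0.02 | 0.8 | 0.5 | 0.02 × 0.2 × 109.4 / 0.5 = 0.875 | 0.152 |
| 0.05 | 0.8 | 0.5 | 0.05 × 0.2 × 109.4 / 0.5 = 2.188 | 0.272 |

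The first and last rows are the extremes of the assumed ranges. If ICC × (1 − CAC) = 0, the ratio is 0 and the error returns to 5%.

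**4. A check by simulation.** Baseline-to-end change was simulated with no intervention effect, 132 pupils per school and an assumed pupil SD of 1.5 on the logit scale. The rejection rate was 0.049 with no school-specific change. It was 0.10, 0.16 and 0.32 with school-change SDs of 0.2, 0.3 and 0.5 on the logit scale. The pattern agrees: stable school differences do no harm, and school-specific change does.

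**The case against.** The best defence is that the primary analysis is not a plain comparison of schools at the end of the year. The baseline is taken before the interventions start, the model tests the interaction with time, and stable differences between schools drop out. This stands. A reader might infer that no valid 5% test exists at all, or that the effect cannot be separated from the school in any sense. The article does not support that reading. A pupil-level test is a fair description of whether these three schools changed differently. It is also valid for an intervention effect if school-by-time variance is zero. The difficulty is that this condition cannot be examined here.

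A related temptation is to quote the inflation from a comparison that ignores baseline, about 13% to 48% for ICC 0.005 to 0.05 with 132 pupils per school. That is not the planned test and should not be used.

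The 9% to 27% is itself open to objection. It rests on three assumed quantities and on two waves, whereas the plan has three waves and continuous time. It is an illustration, not an estimate for the planned model.

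Some sources of school-specific change are also narrowed. The Intervention section says the new dishes use foodstuffs common to all municipal schools, and Data collection at school keeps the control and intervention 1 schools on the same municipal menus. Other sources remain.

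Finally, the article describes the allocation openly and does not present itself as a replicated cluster trial, and the Abstract's wording is hedged. Renaming the design is thus a matter of taste. It cannot be answered, however, that an unseen analysis plan may solve the problem. A random school effect, GEE or robust standard errors cannot recover between-school variance from one school per arm, and the conclusion at issue is printed in this article.

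**Conclusion.** The point holds in a limited form. School-specific change during 2019 is fully aliased with the intervention, and the design offers no means of estimating it. The nominal 5% level applies to an intervention effect only under zero school-by-time variance. Under the assumed ICC, CAC and within-pupil correlation, a two-wave version of the test would have a true type I error of about 9% to 27%. These values are assumptions, and the size would change with them.

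The main Discussion's claim that an accepted hypothesis "will attest to the effect of implementing interventions throughout the public school system of Sumidouro, as well as the country" does not follow. It would need school-to-school variation to be measured, and three schools in three arms do not measure it. The Abstract makes the same extrapolation more cautiously and needs only to be brought into line.

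**What to change.** 1. **Statistical analysis:** state that p-values and intervals describe differences in change between these three schools and do not include school-to-school variation.
2. **Discussion:** replace the claim that the result "will attest to the effect of implementing interventions throughout the public school system of Sumidouro, as well as the country" with wording such as *preliminary evidence from three schools*, and align the Abstract's softer sentence with it.
3. **Sensitivity analysis:** report the main contrast once more with a school-by-time variance added, stating both the ICC and the CAC (for example ICC 0.02 to 0.05 and CAC 0.8 to 0.9). An ICC range alone is ambiguous. In the formula above with 109.4 pupils, ICC 0.01 with CAC 0.9 and ρ = 0.3 gives about 7%. Reading 0.01 to 0.05 as the school-by-time fraction itself gives about 22% (0.01, ρ = 0.3) to 57% (0.05, ρ = 0.5).

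Clustering standard errors on class is not a remedy, because it leaves school-by-time change untouched.

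The cost is one extra analysis and a less favourable conclusion. No new data are required.
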